## Abstract

**Background:**

There are 7000 new cases of head and neck squamous cell cancers (HNSCC) treated by the NHS each year. Stage III and IV HNSCC can be treated non-surgically by radio therapy (RT) or chemoradiation therapy (CRT). CRT can affect eating and drinking through a range of side effects with 90 % of patients undergoing this treatment requiring nutritional support via gastrostomy (G) or nasogastric (NG) tube feeding.

Long-term dysphagia following CRT is a primary concern for patients. The effect of enteral feeding routes on swallowing function is not well understood, and the two feeding methods have, to date, not been compared to assess which leads to a better patient outcome.

The purpose of this study is to explore the feasibility of conducting a randomised controlled trial (RCT) comparing these two options with particular emphasis on patient willingness to be randomised and clinician willingness to approach eligible patients.

**Methods/design:**

This is a mixed methods multicentre study to establish the feasibility of a randomised controlled trial comparing oral feeding plus pre-treatment gastrostomy versus oral feeding plus as required nasogastric tube feeding in patients with HNSCC. A total of 60 participants will be randomised to the two arms of the study (1:1 ratio). The primary outcome of feasibility is a composite of recruitment (willingness to randomise and be randomised) and retention. A qualitative process evaluation investigating patient, family and friends and staff experiences of trial participation will also be conducted alongside an economic modelling exercise to synthesise available evidence and provide estimates of cost-effectiveness and value of information. Participants will be assessed at baseline (pre-randomisation), during CRT weekly, 3 months and 6 months.

**Discussion:**

Clinicians are in equipoise over the enteral feeding options for patients being treated with CRT. Swallowing outcomes have been identified as a top priority for patients following treatment and this trial would inform a future larger scale RCT in this area to inform best practice.

**Trial registration:**

ISRCTN48569216

## Background

Over 7000 new head and neck squamous cell cancers (HNSCC) are treated by the NHS every year. Patients with oropharyngeal HNSCC form the major group of patients who will be eligible for this research project. The incidence of oropharyngeal cancer in the UK has more than doubled in the 10 years between 1995 and 2006 [1]. In Scotland, oropharyngeal cancer is the fastest rising of all cancers [2]. In the USA, it is estimated that in 2020, oropharyngeal cancer will be more common than cancer of the uterine cervix [3].

Advanced (stages III and IV) HNSCC are now treated non-surgically by radiation therapy (RT), or chemoradiation therapy (CRT). In CRT, chemotherapy is delivered concurrently with RT, potentiating not only tumour kill but also toxicity, consequently profoundly affecting eating and drinking by causing a range of side effects: loss of taste, dry mouth, pain, loss of appetite and impaired swallow mechanism. Over 90 % of patients receiving this treatment option need nutritional support for severe dysphagia and weight loss both during and after treatment. When necessary, nutritional support can be delivered through a pre-treatment gastrostomy (G) tube or nasogastric (NG) tube feeds.

Some clinicians advocate that patients with adequate pre-treatment swallow function and oral intake have pre-treatment G tubes and continue with oral diet during treatment until they are no longer able to take adequate amounts of oral diet to maintain nutritional status. Conversely, others offer patients with adequate pre-treatment swallow function the option of continued oral feeding, until they are unable to take adequate oral nutrition to maintain nutritional status and then proceed with (reactive) passage of an NG tube as and when necessary [4, 5]. Generic guidance suggests that G tubes should be placed in patients that need enteral tube feeding for more than 4 weeks [6]. Approximately 2500 gastrostomies are performed for HNSCC patients in the UK. The insertion costs alone are approximately £3 million per annum.

G-tube placement is an invasive procedure with a small but defined risk of acute serious complications [7]; 25 to 35 % of patients retain the tube for >1 year after CRT, 10 % >2 years [8], although recent studies show reduced dependence rates [9] A G-tube has a major impact on patients’ and carers’ quality of life (QoL) [10, 11], due to leakage, soiling of clothes, and interference with family life, intimate relationships and hobbies [12]. While NG tube placement is relatively simple, the smaller diameter tube makes it prone to blockage, thus needing repeated replacement. When care is not taken to ensure correct placement, NG tube misplacement in the lungs and subsequent feeding can lead to significant morbidity, now categorised as a ‘never event’ by the Department of Health [13]. Systematic reviews fail to demonstrate evidence for functional, nutritional, quality of life or health economic benefit of either approach [14, 15]. UK practice is correspondingly variable and no robust data are available [16]. Both NG and G tube users need community support, with greater needs for NG tube users. The National Patient Safety Agency recommends that a full multidisciplinary supported risk assessment should be made and documented, before a patient with a nasogastric tube is discharged from acute care to the community. There is evidence that clinicians in some areas opt for G-tubes due to barriers to the delivery of NG tube nutritional support in the community. However, a recent British Society of Gastroenterology survey showed that only 64 % of G-tube services offer an aftercare service [17].

Long-term dysphagia is now recognised as the principal functional consequence of CRT for HNSCC, and patients report this as a top concern [15, 18]. Dysphagic patients and those dependent on tube feeds (G and NG tubes) need significant long-term supportive care and suffer from impaired quality of life [10]. The effect of either enteral feeding route on the swallowing outcome is not well understood. Gastrostomy placement reduces the need for the patient undergoing CRT to swallow to maintain nutrition. Thus, it is likely that patients using gastrostomy tubes experience a reduction in use of the swallowing musculature. This reduction combined with the mucositis caused by radiation has been hypothesised to increase the risk of fibrosis in the muscles and pharyngoesophageal stricture.

The most severe CRT reaction that causes dysphagia is complete closure of the gullet, devastating for the individual and with substantial costs for the NHS. While this risk may be higher with G-tube use, which bypasses the gullet, unlike an NG tube which maintains a degree of oesophageal patency, G-tube use is associated with shorter hospital stay and fewer hospital admissions [19]. Reconstruction requires complex major reconstructive surgery of the upper aerodigestive tract—with direct care costs of ≈£32,000 per patient [20] and a significant morbidity for the patients involved. There are national guidelines recommending that the proportion of HNSCC patients treated by intensity modulated radiation therapy (IMRT) be increased [21]. However, with respect to swallowing outcomes, IMRT has been shown to increase stricture rates 3.3 times [22]; up to 46 % of HNSCC patients treated by IMRT may needed oesophageal dilatation [23], an intervention that needs inpatient care, is distressing to the patient and is associated with complications.

A systematic review [15] has suggested that feeding route during treatment may impact on the swallow performance after CRT. Four retrospective studies [24–27] one prospective study [28] and one randomised controlled trial (RCT) (with small patient numbers) [29] have identified that swallowing difficulties are more prevalent in patients receiving a prophylactic G-tube, even in the long term. However, existing research on the association of early G-tube feeding and long-term swallow impairment has been inconclusive due to small participant numbers, by the use of insensitive dysphagia measurements and by limited long-term follow-up. The sole RCT [29] recruited from a single Australian centre in an area of low population density. A Cochrane review [14] identified no further eligible trials and concluded that there was insufficient evidence to determine the optimal method of enteral feeding for patients with HNSCC receiving RT or CRT.

These two methods have never been properly compared to establish which leads to better outcomes for patients, despite calls for better information to guide patient and clinician decisions [14, 24, 29]. We therefore wish to conduct a RCT to compare the two feeding methods (pre-treatment gastrostomy versus oral feeding plus as-needed nasogastric tube) in patients with no or only minimal swallowing problems. A similar trial in Australia [29] failed to recruit enough patients; hence, we wish to first carry out a feasibility study to see whether a RCT is possible and inform how it should be conducted.

## Methods/design

### Aims and objectives

Our aim is to determine whether a definitive RCT is feasible in head and neck cancer patients with minimal swallowing problems undergoing CRT comparing oral feeding plus prophylactic gastrostomy tube feeding versus oral feeding plus as-needed nasogastric tube feeding (TUBE study). The TUBE study feasibility phase is a necessary prelude to a full trial of these complex interventions, to assess (i) whether an adequate proportion of eligible patients can be recruited into the study and (ii) whether an adequate proportion of patients comply with the trial protocol including outcome measure completion, according to both quantitative and qualitative data.

The objectives are:A.To explore barriers and facilitators to trial implementation and to use this information to improve recruitment and retentionWillingness of participants to be randomised, to accept and persist with allocated treatment and comply with assessments.Willingness of clinicians (including clinical oncologists, surgeons, nutritionists, speech and language therapists) to recruit patients.Qualitative assessment of patient and carer perspectives on trial participation, barriers to randomisation among non-participants, acceptability of assessment tools and experience of the tube feeding, conduct and compliance of the trial protocol and reasons (and characteristics) of patients dropping out.
B.To carry out preliminary estimation of key parameters to inform definitive study design and study processesConfirm primary outcome measure and associated power/sample size for definitive trial: dysphagia related quality of life as measured by MD Anderson Dysphagia Inventory (MDADI) HNSCC-specific self report scale (variation and differences in change from baseline at 6 months).Trial our subsidiary QoL outcomes (the European Organization for Research and Treatment of Cancer questionnaires EORTC QLQ-C30, EORTC QLQ - H&N35), short form 36 (SF-36) a multi-purpose, short-form health survey and data collection tools for use of health and personal social services and patient costs.Monitor nutritional parameters: body mass index, weekly weight changes (during treatment) and quantity of enteral nutrition consumed.Derivation of an algorithm for when NG tube should be placed in the oral intake arm that is acceptable to patients and nutritionists.

C.Provide health economics metricsAssess economic value of information based upon a modelling exercise informed by the feasibility study and the existing systematic reviews.Provide preliminary estimate of the costs, effects and relative cost-effectiveness of the alternative methods of nutritional support based upon the modelling exercise.

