### Design

A mixed methods multicentre study to establish the feasibility of a RCT of feeding methods in patients with stages III and IV head and neck cancer receiving CRT with curative intent. The work will be conducted over 24 months.

The components are:A multicentre randomised controlled pilot feasibility trial comparing oral feeding plus pre-treatment gastrostomy versus oral feeding plus as required nasogastric tube feeding in patients with HNSCC. Patients will be randomised on a 1:1 basis and stratified by IMRT and by the treating centre.A qualitative process evaluation to inform the trial design by investigating patient, carer and staff experiences of trial participation.A modelling exercise to synthesise available evidence and provide preliminary estimates of cost-effectiveness and value of information from future research.

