### Statistical considerations

Target recruitment is 60 patients (30 per arm of the study) [34]. As a feasibility study, we will provide an assessment of recruitment and compliance rates to inform future trial design. Statistical analyses are according to a confidence interval rather than a hypothesis testing approach. Analyses will be descriptive reporting rates as proportions with confidence intervals and graphical analyses of longitudinal data. Recruitment is dependent on the number of patients approached but should be no lower than 50 %. The upper limit of the 95 % confidence interval for the proportion of patients recruited should exceed 50 %. If 120 patients were approached and 50 % were recruited (60 patients randomised), the 95 % confidence interval for the recruitment rate would have width ±9 %. This would provide a good level of accuracy to assess the acceptability of the recruitment rate.

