### Progression criteria to phase III trial

The decision to move to a phase III trial will be based on:Adequate timely recruitment with a 50 % recruitment rate.Completeness of outcome measurement (MDADI at 6 months): excluding those individuals who die during the study period. This outcome data successfully collected should be greater than or equal to 80 %, as this will be the primary outcome for the planned phase III trial.Economic criteria of EVOI to suggest further research likely to be worthwhile.

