## Discussion

### Potential impact of the trial

Our national survey [16] shows that clinicians working in this field are in equipoise regarding the feeding route to be used in patients receiving chemoradiation for head and neck cancer. The survey concluded that in the absence of a national consensus on which patients to recommend for gastrostomy, consideration should be given to the development of clinical decision-making models in an attempt to systematise the decision-making process.

Clinicians have looked at this issue in a paper published in 2001 [24], when a robust study was called for in this field. Since then, Cochrane reviews [14] and other prospective and retrospective studies [25, 27–29] have been published, indicating that there is an appetite to progress the science in this area. By using swallowing outcomes as our primary measure, we are focusing on an outcome that patients tell us as being important issue [18]. Thus, if this trial finds evidence to support a change in clinical practice, such findings will have the required impact. It is worth noting that if the change in practice were to support the non-surgical (oral + NG tube) arm, there may be reductions in morbidity and mortality caused by the interventions. There may also be potential cost savings in the non-surgical arm but this may be offset by the cost of repeat return to hospital for re-siting NG tubes, radiologic examinations, and the cost of district nursing support with NG tubes which is not always required with G tubes. In addition, some of the generic conclusions on the patient and carer experiences of tube feeding will be applicable to other areas of medicine. Thus, research on this area may serve to direct resources appropriately, reduce unnecessary interventions and thus reduce morbidity, mortality and improving swallowing outcomes. Irrespective of the effect size the TUBE study demonstrates, the project will generate a great deal of invaluable comparator information about the two treatments which can inform patient contribution to future shared decision-making. Our integrated qualitative study will draw on the theoretical framework of normalisation process theory [35] to identify the barriers and facilitators to changing clinical practice in this field.

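### Objective B lists the pilot's MDADI difference, beside its variation, as an input to the definitive sample size, but about 24 to 30 patients per arm estimate that difference too imprecisely for this use

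*Protocol article*

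**What the plan says.** Under Aims and objectives, objective B of the protocol article sets out to confirm the primary outcome of the definitive trial and its power and sample size. In brackets after the MDADI it names what will be used: "variation and differences in change from baseline at 6 months". The words between arms do not appear, but a difference that feeds the power of a two-arm trial is naturally the between-arm one. The lead-in to objective B calls these estimates preliminary.

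The size of the pilot is given under Statistical considerations: "Target recruitment is 60 patients (30 per arm of the study". The Design section states "Patients will be randomised on a 1:1 basis and stratified by IMRT and by the treating centre". Under Progression criteria, 6-month MDADI completeness is judged "excluding those individuals who die during the study period", and "This outcome data successfully collected should be greater than or equal to 80" per cent.

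On analysis, the article says "Statistical analyses are according to a confidence interval rather than a hypothesis testing approach". It works out precision for one quantity only, the recruitment rate. The economic section adds that value-of-information findings, together with other information, will help to determine the size of the later trial.

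**The concern.** The bracket puts two quantities of very different quality side by side. A pilot of this size estimates an SD reasonably well. It estimates a treatment difference poorly, and required sample size varies with one over the difference squared, so the error is magnified. If the observed difference is used as the effect size, a chance high value gives an underpowered definitive trial and a chance low value gives a needlessly large one. What is at stake is the design of the later trial. The conduct of this study, its feasibility outcome and its progression decision are not affected.

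**Working it through.** **The article's own precision figure.** It starts from "If 120 patients were approached and 50 % were recruited (60 patients randomised") and states ±9 %. The half-width is 1.96 × √(0.5 × 0.5 / 120) = 0.0895, so the figure reproduces.

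**Inputs for the MDADI difference.** There are 30 per arm (Statistical considerations). At the 80 % completeness threshold (Progression criteria), 0.80 × 30 = 24 per arm. Deaths are outside that denominator, so the number analysed could be lower still. Assumptions not in the article: true difference 0.3 to 0.6 SD, SD of change 15 to 25 MDADI points, two-sided 5 %, 90 % power.

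**Precision of the difference.** Half-width = t(2m − 2) × √(2/m), in SD units.
- m = 24: 2.013 × 0.289 = 0.58 SD
- m = 30: 2.002 × 0.258 = 0.52 SD

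For assumed SDs of 15, 20 and 25 points, this is ±8.7, ±11.6 and ±14.5 points at 24 per arm, and ±7.8, ±10.3 and ±12.9 points at 30 per arm.

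**Precision of the SD.** The chi-square 95 % limits are 0.83 to 1.26 times the estimate (46 df) or 0.85 to 1.22 times (58 df).

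**What one standard error does to the planned size.** n per arm = 2 × (1.960 + 1.282)² / d². Take a true difference of 0.4 SD and 24 per arm.
- Correct d = 0.4: 131.3, so 132 per arm
- One SE high, d = 0.689: 44.3, so 45 per arm
- One SE low, d = 0.111: about 1,700 per arm

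**Chance of an underpowered definitive trial if the observed difference is plugged in.** True power falls below 80 % when the pilot estimate exceeds the true difference by the factor (1.960 + 1.282)/(1.960 + 0.842) = 1.157. Take 0.4 SD, 24 per arm and a known SD. The chance of exceeding that factor is 1 − Φ(0.157 × 0.4 / 0.289) = 0.414. The chance of a positive estimate is Φ(0.4/0.289) = 0.917. The ratio is 0.45. Simulation with the SD estimated as well gives, among pilots with a positive difference:

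| True difference (assumed) | 24 per arm | 30 per arm |
|---|---|---|
| 0.3 SD | 51 % | 49 % |
| 0.4 SD | 46 % | 43 % |
| 0.5 SD | 41 % | 39 % |

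At 0.4 SD and 24 per arm, a further 8 % of pilots show a difference of the wrong sign. Counting all pilots regardless of sign, over 0.3 to 0.6 SD, the share below 80 % power is 36 to 45 %.

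**The alternative: fixed target difference, pilot SD only.** Power falls below 80 % when the pilot variance is under (2.802/3.242)² = 0.747 of the true variance. The chi-square probability is 10 % (46 df) or 8 % (58 df). Simulation with whole-number sizes gives about 7 to 10 %.

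**Spread of the planned size at a true 0.5 SD (correct n = 85 per arm).**

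| Method | Middle 80 % of planned n, m = 24 | m = 30 | Below half the correct n | Above double |
|---|---|---|---|---|
| Observed difference and SD | 27 to 941 | 30 to 680 | 22 to 25 % | 28 to 30 % |
| Fixed difference, pilot SD | 63 to 108 | 65 to 105 | under 0.2 % | under 0.2 % |

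**The case against.** The strongest reply is that one word is being made to carry too much. The estimates are called preliminary. To confirm a sample size can mean checking an existing assumption. The economic section brings in value-of-information findings and other information. No rule makes the size a function of the observed difference, and every consequence computed here assumes such a rule. An article may also leave the target difference to the full protocol or the SAP, so its absence is not charged. All of this stands, and it limits the point to what could happen. Even under plug-in use at a true 0.5 SD, 45 to 50 % of planned sizes lie between half and double the correct one. It does not remove the point, because the difference is still named as an input and nothing in the article withdraws it.

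Two stronger readings are tempting but not supported. A reader might infer that a low observed difference would stop the definitive trial. The progression criteria are recruitment, MDADI completeness and the economic value of further research. The observed difference is not among them, and the economic model takes its probabilities mainly from existing reviews and literature. A reader might also infer that the Discussion treats the observed effect size as valuable evidence. Its sentence reads "Irrespective of the effect size the TUBE study demonstrates, the project will generate a great deal of invaluable comparator information about the two treatments", which says that the information follows whatever the effect size is, and makes no link to sample size. That sentence needs no change on this ground.

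The confidence-interval approach already implies that any arm difference will be shown with its uncertainty, which reduces the risk of over-interpretation.

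**Conclusion.** The point holds in limited form. Objective B names the pilot difference as one input to the definitive sample size, and 24 to 30 patients per arm cannot supply it with useful precision. The interval widths in SD units follow from the article's own numbers. The comparison of 39 to 51 % with 7 to 10 % rests on assumed true differences of 0.3 to 0.5 SD, two-sided 5 %, 90 % power, and direct use of the observed difference. The ordering of the two methods is the same at every value examined. This is a worthwhile correction to the planning of the later trial and leaves the feasibility conclusions intact.

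**What to change.** In objective B, remove the difference in change from baseline as an input to sample size. State that the target MDADI difference will be a minimum important difference justified from outside the pilot, and that it will be fixed before outcomes are seen by arm. From the pilot, take only the SD of the MDADI outcome, the correlation with baseline, and completeness. Report the arm difference descriptively with its confidence interval, as the Statistical considerations section already implies.

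Say how the uncertainty of the SD will be allowed for. Planning on an upper confidence limit is one option. The upper 80 % limit is about 1.10 times the estimate at 46 df, so the definitive trial would be about 1.10² = 1.21 to 1.22 times as large. That is a trade-off for the trial team and not a requirement.

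The change costs wording only. Data collection, analysis and progression criteria for this study stay as they are. The article reports the trial as recruiting and in follow-up, so the target difference can be recorded in the SAP or a dated note if outcomes have not yet been seen by arm.

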### Target population

The target population will be patients with stage III and IV HNSCC who receive primary CRT with curative intent.

Inclusion criteria:

(1) Grade 1 pre-treatment dysphagia, as defined by Common Terminology Criteria for Adverse Events v4.0 (defined as asymptomatic/symptomatic/able to eat regular diet). (2) Consent to be randomised.

Exclusion criteria:

Patients who (1) decline to participate, (2) are unable to give informed consent, (3) cannot receive a gastrostomy for medical reasons, (4) do not receive treatment with curative intent and (5) patients with malnutrition requiring immediate initiation of enteral feeding.

Clinical experience suggests that patients with primary sites in the oropharynx, larynx, nasopharynx and unknown primaries are those who will fulfil the inclusion criteria (~35 to 40 % of all HNSCC patients).

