### Outcomes measures

The primary outcome of feasibility will comprise of the following entities:Willingness of patients to be randomised (assessed via review of patient screening logs) defined as:i.The number of patients consenting to be randomised as a proportion of all patients approached about the trial, with reasons for non-consentii.Qualitative assessment of barriers and facilitators to recruitment
Willingness of clinicians to randomise patients—assessed via qualitative interviewsAssessment of retention and drop-out rates, defined as:i.The number of patients who start randomised treatment as a proportion of the number randomised, with reasons for early drop outsii.The number of patients who complete randomised treatment as a proportion of the number randomised, with reasons for drop outs (including death)iii.Completeness of MD Anderson Dysphagia Inventory (MDADI) assessment within 6 monthsiv.Qualitative assessment of barriers and facilitators to data collection and participant retention

Secondary outcome measures are:

The following scores/ measures will be requested at baseline (before treatment) and at 3 and 6 months after treatment (5 and 8 months from randomisation):A.The MDADI is a self-administered questionnaire designed specifically for evaluating the impact of dysphagia on the quality of life of patients with head and neck cancers [30]. This will be our primary outcome measure in the full trial.B.Quality-of-life outcomes

We will use two questionnaires to assess quality of life outcomes. The European Organization for Research and Treatment of Cancer questionnaire EORTC QLQ-C30 (version 3.0) is a cancer-specific instrument, has a multidimensional structure, appropriate for self-administration and is applicable across a range of cultural settings [31]. The EORTC QLQ - H&N35 is the head and neck module for EORTC QLQ-C30 (version 3.0) and is intended for use in conjunction with the QLQ-C30 in patients with head and neck cancer [32].C.Short form 36

The SF-36 is a multi-purpose, short-form health survey with 36 questions. It yields an eight-scale profile of functional health and well-being scores as well as psychometrically based physical and mental health summary measures and a preference-based health utility index that will be used to derive quality-adjusted life-years for a cost-utility analysis conducted as part of a subsequent full trial.D.Use of health and personal social services and costs to patients and their families/carers

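### Objective B sizes the definitive trial on the variation in MDADI change from baseline; this can never give a smaller trial than the baseline-adjusted 6-month score, and may give a larger one

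*Protocol article*

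**What the plan says.** Protocol article, Aims and objectives, objective B: one purpose of the pilot is to confirm the primary outcome of the definitive trial and its power and sample size. The MDADI quantity named for this is "variation and differences in change from baseline at 6 months". No other MDADI basis for sizing appears, and adjustment for baseline is not mentioned.

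Other sections describe the same endpoint without a change score. Outcomes measures says of the MDADI: "This will be our primary outcome measure in the full trial". Progression criteria to phase III trial has "Completeness of outcome measurement (MDADI at 6 months" and then refers to it as the primary outcome of the planned phase III trial.

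The data needed for either approach will exist. The Outcomes measures section says that the MDADI and the other scores "will be requested at baseline (before treatment) and at 3 and 6 months after treatment (5 and 8 months from randomisation". The Design section stratifies randomisation by IMRT and by treating centre.

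**The concern.** One of the pilot's stated tasks is to hand a measure of MDADI variability to the definitive trial. The measure named is the variation of the change score. Subtracting baseline in full assumes a slope of 1 of the 6-month score on baseline. Baseline adjustment (ANCOVA) estimates that slope instead, so its residual variance cannot be larger. If the pilot reports only the SD of the change, a later designer cannot recover the ANCOVA residual SD, because that also needs the 6-month SD and the correlation.

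A larger definitive trial than necessary would matter here. The Background section says that a similar Australian trial failed to recruit enough patients, and adequate, timely recruitment is itself a progression criterion.

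**Working it through.** **The plan's own figures.** The article states no MDADI SD, correlation, target difference or definitive sample size, so there is no MDADI figure to reproduce. The one precision figure under Statistical considerations concerns recruitment: 1.96 × √(0.5 × 0.5 / 120) = 0.0895, which agrees with the stated ±9 %. It does not bear on this point.

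**Notation.** s0 = baseline SD, s1 = 6-month SD, r = their correlation (all within arm and taken as equal across arms), k = s0/s1. All values of k and r below are assumptions.

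**Formulae.**
- Variance of unadjusted change: s0² + s1² − 2·r·s0·s1 = s1²(1 + k² − 2rk)
- ANCOVA residual variance: s1²(1 − r²)
- Difference between them: (s0 − r·s1)², which is never negative and is zero only when r = k
- Under randomisation both approaches target the same mean difference between arms, so the ratio of sample sizes is (1 + k² − 2rk)/(1 − r²)

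**Ratio of sample sizes, change score to ANCOVA.**

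| k | r = 0.2 | r = 0.3 | r = 0.5 |
|---|---|---|---|
| 0.5 | 1.05/0.96 = 1.09 | 0.95/0.91 = 1.04 | 0.75/0.75 = 1.00 |
| 0.7 | 1.21/0.96 = 1.26 | 1.07/0.91 = 1.18 | 0.79/0.75 = 1.05 |
| 1.0 | 1.60/0.96 = 1.67 | 1.40/0.91 = 1.54 | 1.00/0.75 = 1.33 |

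**In patients.** Assume a difference of 0.5 × s1, two-sided 5 % and 80 % power. Then n per arm = 2 × (1.96 + 0.84)² × (variance/s1²)/0.5², or about 62.8 × variance/s1². At r = 0.3, ANCOVA needs 62.8 × 0.91, that is 58 per arm. The change score needs 60 (k = 0.5), 68 (k = 0.7) or 88 (k = 1).

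**Pilot sampling error.** The pilot target is 60. With 80 % complete there would be 48 pairs and 46 degrees of freedom. The 95 % interval for the true variance over the estimated variance is then about 0.69 to 1.58, whichever scale is used.

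**The case against.** The strongest reply is that the article does not commit the definitive trial to an unadjusted change-score analysis. The wording is a parenthesis under an objective described as preliminary estimation, two other sections do not speak of change, and no analysis model is stated. Change from baseline can also be analysed with baseline as a covariate, which gives the same treatment estimate and standard error as ANCOVA on the 6-month score. All of that stands, so a reader who infers that an unadjusted change analysis is fixed goes beyond the text. It does not remove the point. Even when change is analysed with baseline as a covariate, the SD needed for sizing is the residual SD, and objective B names the variation in change.

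A second reply is that baseline adjustment belongs in an analysis plan. As a bare omission it would be no finding. Here, however, the article itself chooses the quantity for sizing.

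A third reply concerns size. Eligibility is limited to Grade 1 dysphagia, with patients "able to eat regular diet". If that makes baseline MDADI narrow, k is below 1 and the equal-SD row of the table is the least relevant. Subtracting baseline does not always add noise either: at k = 0.5 and r = 0.3 the change variance is 0.95 of the 6-month variance. Both a narrow baseline and a low correlation are inferences, since the criterion is a dysphagia grade and the MDADI is self-reported. This limits the size of the penalty but not its direction.

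Pilot sampling error is comparable with or larger than the penalty in the narrow-baseline rows. But it runs both ways and cannot be avoided, whereas the choice of scale can.

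A reader might also infer that chance baseline imbalance or regression to the mean harms the pilot's own results with 30 per arm. That has little force: "Statistical analyses are according to a confidence interval rather than a hypothesis testing approach", the primary outcomes are recruitment and retention, and randomised arms share regression to the mean in expectation.

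**Conclusion.** The point holds as a recommendation on a stated choice, not as an error in a stated figure. Sizing the definitive trial on the SD of the unadjusted change can never give a smaller trial than sizing on the baseline-adjusted 6-month score (leaving aside the degree of freedom spent on the slope), and may give a larger one. For r between 0.2 and 0.5 the excess is about 0 to 9 % at k = 0.5, 5 to 26 % at k = 0.7 and 33 to 67 % at k = 1.

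It is tempting to conclude that the derived size will be too large, or to quote 67 % as the penalty. The documents support neither. They give no SD, correlation, target difference or sample size, the penalty is zero when r = k, and 67 % needs equal SDs with r = 0.2. The economic modelling section adds that value-of-sampling results and other information will also inform the size. Nothing here affects the pilot's feasibility outcomes.

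**What to change.** In objective B, replace the change-score wording with: *6-month MDADI adjusted for baseline MDADI and the stratification factors (IMRT, centre)*. This also brings it into line with the progression criteria.

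State that the pilot will report, with confidence intervals, the baseline SD, the 6-month SD, the correlation between baseline and 6 months, and the ANCOVA residual SD. Base the MDADI component of the definitive sample size on the residual SD. The SD of the change can still be reported as a description.

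The cost is a change of wording and a few extra lines of output. Baseline and 6-month MDADI and both stratification factors are already part of the design, so no added data, visits or patients are needed.
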